### Sample size considerations

#### Phase 1

Participants for Phase 1 will be recruited until data saturation is achieved, that is, when the interviews no longer provide new information or knowledge to the researchers about an AMD patient’s perspective on participating in the MINGLE program. According to our previous research investigating the barriers and facilitators to participating in a mental wellbeing program among people with AMD [34], approximately 30 participants were required to achieve this.

#### Phase 2

A minimum of 52 participants are required to achieve a pre-post change in the primary outcome (i.e., loneliness), assuming a 0.4 effect size according to Cohen’s d and 80% power (G*Power 3.1 software). An effect size of 0.4 was chosen as the average effect size of our previous WTL-related work i.e., 0.43 [35] and 0.35 [16] for loneliness using the De Jong Gierveld Scale. The later study also proved to be feasible and acceptable demonstrating ≥ 80% adherence rate, 88% retention rate and was acceptable or highly acceptable by ≥ 95% of participants [16].

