**Methods and analysis:**

Phase 1 involves AMD patients who will be recruited from an eye clinic in Western Sydney, Australia to participate in audio-recorded semi-structured interviews. Verbatim interview transcripts will be coded using the Capability, Opportunity, Motivation and Behaviour (COM-B) model and themes established. These themes will be used as a guide to specifically tailor the proposed MINGLE program to people with AMD. Phase 2 involves 52 AMD patients who will then be recruited from the same clinic to participate in the MINGLE program. Pre-post questionnaires will be administered to intervention participants to collect information on the following variables: demographics, socioeconomic status, vision function, loneliness, quality of life (including depression), falls risk, physical activity (level), and dietary intake. The acceptability and feasibility of the MINGLE program will also be evaluated using descriptive statistics.

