**Fig 1 pone.0267581.g001:**
[figure not shown]
MINGLE pilot trial schedule of enrolment, interventions, and assessments.

#### Phase 1

Participants for the semi-structured interviews will be recruited over three months or until data saturation is achieved. Interviews will be conducted in-person in a private room at the eye clinic or over the telephone depending on the participant’s preference and/or COVID-19 restrictions at the time. The inclusion criteria for Phase 1 are: 1) diagnosis of any form of AMD, 2) fluent English and 3) consent to participate in the study (including audio recording). Patient eligibility and interests will be screened by the researcher who will provide an explanation of the study. Informed verbal consent will be audio recorded and documented in a Record of Verbal Consent form.

#### Phase 2

Recruitment for Phase 2 will commence after the preliminary findings from Phase 1 have been identified. These findings will help to inform any modifications to the MINGLE program prior to conducting the pilot study. Participants will be recruited over six months or until the sample size target of 52 AMD patients is achieved. The inclusion criteria for Phase 2 are: 1) diagnosis of any form of AMD, 2) fluent English, 3) access to a smart phone, tablet or laptop with a front-facing camera; 4) technical ability to use Zoom or have someone to help; 4) clearance to safely participate in the physical activity components of the intervention (Physical Activity Readiness Questionnaire (PARQ+ [19]) or written physician clearance for participation) and; 5) written informed consent to participate. Specific exclusion criteria for Phase 2 are: 1) best-corrected visual acuity of worse than 6/60 (legal blindness) in both eyes [20]; 2) unable to ambulate/walk for exercise; 3) serious illness (including mental and cognitive illness) limiting their ability to exercise or complete the trial; 4) contraindications to exercise (i.e., failure to fulfil the prerequisites of the PARQ+); 5) uncontrolled hypertension (≥160/>90 mmHg); 6) signs or symptoms of alcohol/substance abuse and; 7) unable to commit to attending ≥80% of the sessions. Participation in Phase 1 of this study is not an exclusion criterion.

### Semi-structured interviews in Phase 1

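### The 52 participants said to give 80% power are 52 complete pre-post pairs, but recruitment stops at 52 enrolled, so any dropout takes power below 80% (minor, wording only)

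*Protocol article*

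**What the plan says.** In the protocol article, Sample size considerations, Phase 2: "A minimum of 52 participants are required to achieve a pre-post change in the primary outcome (i.e., loneliness), assuming a 0.4 effect size". The stated power is 80%, from G*Power 3.1. No significance level, sidedness or test is named, and no allowance for dropout is mentioned.

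Under Recruitment, Phase 2, the same number ends enrolment: "Participants will be recruited over six months or until the sample size target of 52 AMD patients is achieved". The abstract agrees: "Phase 2 involves 52 AMD patients who will then be recruited from the same clinic to participate in the MINGLE program".

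The sample size paragraph also reports how an earlier related study performed: "The later study also proved to be feasible and acceptable demonstrating ≥ 80% adherence rate, 88% retention rate". That study supplied one of the two effect sizes behind the assumed 0.4.

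Two other sections bear on the point. Outcome measurement lists the attrition rate among the things to be evaluated. The Phase 2 analysis plan carries the last observation forward where data are missing and describes the pre-post changes with descriptive statistics.

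**The concern.** A power calculation for a pre-post change gives the number of people who must have both measurements. If that number is also the point at which enrolment stops, the stated power is reached only if nobody is lost. The six-month limit on recruitment can only lower the number further. The protocol does not treat loss as impossible: it plans to measure attrition, has staff prompt participants to return questionnaires, and sets a rule for missing data.

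What is at stake is the accuracy of a stated design property. A reader of a null loneliness result would take it as coming from a comparison with 80% power at a standardised change of 0.4, when the power to be expected is somewhat lower.

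**Working it through.** **Inputs from the protocol article.** Standardised pre-post change d = 0.4; power 80%; n = 52; enrolment stops at 52; 88% retention in the cited earlier study.

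**Assumptions.** Two-sided α = 0.05 and a paired t-test, neither of which is stated. Retention of 95% and 80% is used only to show a range around 88%. No retention rate is planned for this trial.

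**Formula.** For n complete pairs, df = n − 1 and the noncentrality is d√n. Power is the probability that a noncentral t variable with that df and noncentrality falls outside ± the 97.5% point of the central t.

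**Step 1: reproduce the 52.**
- n = 51: noncentrality 0.4 × √51 = 2.857, critical value 2.009, power 0.7999.
- n = 52: noncentrality 0.4 × √52 = 2.884, critical value 2.008, power 0.808.

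The smallest n reaching 80% is exactly 52, with nothing added for loss. A one-sided 5% test would need only 41 pairs, so it does not reproduce the figure without a further unstated step.

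**Step 2: apply loss to 52 enrolled, using completers only.**

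| Retention | 52 × retention | Pairs used | Noncentrality | Power at d = 0.40 |
|---|---|---|---|---|
| 100% | 52 | 52 | 2.884 | 80.8% |
| 95% | 49.4 | 49 | 2.800 | 78.3% |
| 88% | 45.8 | 46 | 2.713 | 75.6% |
| 80% | 41.6 | 42 | 2.592 | 71.6% |

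A single loss (51 pairs) already gives 79.99%. With 46 pairs, the change detectable with 80% power is 0.42.

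**Step 3: apply the planned carry-forward rule.** With one measurement before and one after, a dropout's baseline is carried forward and the change is zero. Take 46 real changes (mean 0.4, SD 1) and 6 zeros among 52:
- mean = 0.4 × 46/52 = 0.354
- variance = 46/52 + (46/52)(6/52)(0.4²) = 0.885 + 0.016 = 0.901, so SD = 0.949
- effective d = 0.354 / 0.949 = 0.373
- noncentrality = 0.373 × √52 = 2.69, against 2.71 for the 46 completers alone

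Simulation (100,000 replicates) gives 75.8% power with exactly 6 zeros, and 75.5% when each participant is lost with probability 12%. All 52 are nominally analysed, but the zeros dilute the mean change and power is again about 76%.

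**The case against.** **The setting.** This is a single-group pilot whose purpose is acceptability, feasibility and preliminary efficacy. The analysis section describes the loneliness change rather than testing it, and Outcome measurement lists loneliness among the secondary outcomes although the sample size paragraph calls it primary. Moving from 80% to 76% power, or from a detectable change of 0.40 to 0.42, would hardly alter how a pilot result is read. This stands, and it sets the importance of the point. It does not make the stated figure right: the protocol chose to give a power and a required minimum, and elsewhere it looks for a significant reduction in loneliness.

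**The 88%.** A reader might infer that the protocol itself plans for 88% retention and then ignores it. The text does not support that. The rate is a result of an earlier study, described in the Introduction as one in older adults with hearing loss, and it is quoted as evidence of feasibility. The present trial excludes people who cannot commit to at least 80% of sessions and prompts questionnaire return, so its retention may differ. Hence the range above; the direction holds for any loss at all.

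**The test.** Two-sided 5% is inferred. At one-sided 5%, 46 pairs would give 84.8% power, and 41/0.8 = 51.25 also rounds up to 52. That route needs both an unstated one-sided test and an unstated 20% loss. The two-sided reading needs only the usual default and lands on 52 directly. It is the more likely, but remains an assumption.

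**The effect size.** A reader might also count it as an error that the two cited values, "0.43 [35] and 0.35 [16] for loneliness using the De Jong Gierveld Scale", average 0.39 and not 0.4. To one decimal 0.39 is 0.4. This is rounding, and nothing here rests on it.

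**Conclusion.** The point holds as a minor one. Under a two-sided 5% paired t-test, 52 is the uninflated number of complete pairs, and the protocol uses the same number to end enrolment. Any attrition takes power below the stated 80%: about 78%, 76% and 72% at 95%, 88% and 80% retention. Carry-forward does not recover it.

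The conclusion rests on the inferred test and, for the 76% figure, on retention resembling that of the earlier study. A reader might go further and infer that the trial is inadequately sized or must recruit more. At 88% retention, 52 complete pairs would indeed need 52/0.88 = 59.1, so 60 enrolled. But the shortfall from the stated 80% is 4 to 5 points, in a pilot with feasibility aims and a descriptive analysis, and the documents give no ground for requiring a larger study. What needs correcting is the statement, not the design.

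**What to change.** In Sample size considerations, Phase 2, remove the claim that 52 is the minimum required and replace it with wording such as:

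> *52 will be enrolled; if retention is similar to the 88% in the earlier related study, about 46 will have both measurements, giving about 76% power (two-sided 5% paired t-test, and about the same under last observation carried forward) for a standardised mean change of 0.40, or 80% power for 0.42.*

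The sponsor should first confirm the level and sidedness entered in G*Power. If they were not two-sided 5%, the sentence should name the test actually used and the power recalculated for it.

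The cost is wording only. No further participants, visits or analyses are needed, and the stated power becomes slightly less favourable.

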### Data collection and analysis plan

#### Phase 1

Semi-structured interviews will be conducted Data for all participants will be audio recorded and transcribed verbatim using an external transcribing service. Transcripts will be analysed iteratively to ensure analytic reflexivity. Two members of the research team with a vision science and/or ophthalmology background will deductively code the transcripts using content analysis [36] based on the Capability, Opportunity, Motivation and Behaviour (COM-B) model of the behaviour change wheel [37]. Codes will be discussed, and consensus reached with other members of the research team. Themes will be established under each subset of the COM-B model relating to barriers and facilitators to participating in an interactive online program. Phase 1 findings will inform the design of MINGLE.

#### Phase 2

Data for all participants will be collected via online self-report pre-post questionnaires administered via REDCap. Participants will be prompted to complete and return questionnaires by study staff to promote participant retention. All data will be entered into REDCap. Only staff directly involved in the study will have access to the databases. Statistical analysis will be carried out using IBM SPSS Statistics V.25. Descriptive statistics will be used to assess the acceptability and feasibility of MINGLE and the pre-post intervention changes in loneliness, depression, falls self-efficacy, physical activity, and dietary intakes. For missing data, the last observations will be carried forward prior to data analysis.

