Amongst people with AMD, positive participant responses to virtual programs have also been reported in another evidence-based intervention developed by our group, which aimed to improve the dietary intakes of people with AMD through telehealth nutrition intervention [17]. This telehealth intervention involved the provision of an evidence-based workbook on nutrition and AMD links, together with monthly individual phone calls with a dietitian over four months, which significantly improved the participants’ dietary intake of nutrient-rich dark green leafy vegetables and legumes and reduced consumption of packaged and processed foods [17].

To address the impacts of vision loss caused by AMD, including the increased prevalence of loneliness, depression and falls risk, as well as to improve AMD-related lifestyle risk factors (poor diet and physical inactivity), we aimed to build on our prior research by developing a holistic program called MINGLE (Movement, Interaction and Nutrition for Greater Lifestyles in the Elderly) and piloting this novel program in a sample of older Australian adults with AMD. Therefore, this study aims to: 1) develop the MINGLE program tailored to AMD patients, by incorporating the successful aspects of existing evidence-based interventions developed by our group (WTL-Z and a dietary intervention [17]); and 2) deliver the MINGLE program online via Zoom [18] in a non-randomised group of AMD patients. Although our prior research has shown that online delivery of WTL-Z can effectively reduce loneliness and depression, this study was conducted in normal sighted older adults residing in the UK. Hence, this pilot study is needed to evaluate the acceptability and feasibility of delivering the online MINGLE program in visually impaired older adults. The aims of this study will be achieved through two phases. Phase 1 will conduct semi-structured interviews with AMD patients to identify the barriers and facilitators to participating in the proposed MINGLE program; to determine the participants’ thoughts about MINGLE and what they would change or would like included in the program and to accordingly modify the proposed MINGLE program to better suit the needs of people with AMD. Phase 2 will then involve a non-randomised pilot trial of the modified MINGLE program in AMD patients to determine the program’s acceptability and feasibility and its preliminary efficacy.

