### Outcome measurement

Data collected on the abovementioned measures will be used to evaluate the program’s preliminary efficacy and its acceptability and feasibility. Specifically, this includes an evaluation of: 1) recruitment strategies–identifying the reach of each recruitment source; 2) recruitment rates at each stage of the project i.e., total number who expressed an interest in Phase 1 or 2, proportion who were eligible, provided consent, and completed the baseline questionnaire; 3) program adherence based on self-reported adherence and the Research Assistant’s evaluation during each session; 4) attrition rate; 5) pre-post responses to the AFRIS questionnaire; and 6) qualitative data obtained from the feedback survey and focus group discussion immediately post-intervention (Fig 1). The feedback survey includes Likert scales to rate overall satisfaction with the program and adherence to the nutritional advice provided, two Yes/No questions to determine whether participants would recommend the program to a friend and if the program was worthwhile, and two open-ended questions to identify the most useful or valuable components of the program, and for additional suggestions to improve the program.

Secondary outcome measures include participant-specific outcomes including a significant reduction in loneliness according to the De Jong Gierveld Scale, after completion of the 10-week MINGLE program, and significant changes in depression; quality of life; falls self-efficacy; physical activity (level) and overall diet using the AQoL-8D’s mental health dimension, overall AQoL-8D, FES-I, Active Australia Survey, and SDQ-AMD, respectively.

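### Phase 2 is sized for a significance test on loneliness and its participant outcomes are defined by significance, but the analysis section provides only descriptive statistics for them

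*Protocol article*

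**What the plan says.** Three parts of the protocol article bear on this.

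- **Outcome measurement** first lists the feasibility and acceptability evaluations, none of them defined by significance. It then turns to the participants: "Secondary outcome measures include participant-specific outcomes including a significant reduction in loneliness according to the De Jong Gierveld Scale". The sentence continues with significant changes in five more outcomes: depression (the AQoL-8D mental health dimension), quality of life (overall AQoL-8D), falls self-efficacy (FES-I), physical activity (Active Australia Survey) and diet (SDQ-AMD).
- **Sample size considerations, Phase 2** states: "A minimum of 52 participants are required to achieve a pre-post change in the primary outcome (i.e., loneliness), assuming a 0.4 effect size", and adds 80% power from G*Power 3.1. Loneliness is the primary outcome here but sits among the secondary outcomes in the section above. Neither alpha nor sidedness is given.
- **Data collection and analysis plan, Phase 2** is the only text on how Phase 2 data are analysed. It says: "Descriptive statistics will be used to assess the acceptability and feasibility of MINGLE and the pre-post intervention changes in loneliness", and extends this to depression, falls self-efficacy, physical activity and dietary intakes. It names no test, confidence interval or significance level, and quality of life is not on the list.

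**The concern.** A significant reduction is the result of a test, and 80% power is a property of a test. The analysis section assigns these same changes a method that includes no test. The section is not silent on the point, which might be left to a fuller document: it names a method, and that method cannot deliver what the other two sections call for.

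Two outcomes are possible. If the text is followed, the trial reports means and spreads before and after, and the question for which 52 people were recruited goes unanswered. If a test is added later, its form may be settled once the data are visible. On a loneliness scale that runs only from 0 to 6, a paired t-test and a signed-rank test are both plausible, and the published text would not show which was intended.

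**Working it through.** **1. Does 52 come from a test?**

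Inputs from Sample size considerations: d = 0.4, power 80%, one group measured before and after. Assumptions: alpha 5%, and d is the mean change divided by the SD of the change.

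Model: paired t-test on the change, exact noncentral t with n − 1 degrees of freedom and noncentrality d√n.

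- Two-sided 5%, d = 0.4: the smallest n with power of at least 80% is **52**. At n = 52 the noncentrality is 0.4 × √52 = 2.88, the critical value is t(0.975, 51) = 2.008, and power is 80.8%.
- Normal approximation: ((1.960 + 0.842)/0.4)² = 49.1, so n = 50.
- One-sided 5%, d = 0.4: n = 41, which does not match.

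At the stated d, the figure is therefore that of a two-sided 5% paired t-test. Other inputs can also reach 52 (one-sided 5% at d = 0.35, for example), but they are not the inputs the section states.

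**2. How firm is 52?**

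- The two cited effect sizes average (0.43 + 0.35)/2 = 0.39, rounded to 0.4. At 0.39 the exact calculation gives n = 54, and power at 52 is 78.8%. The rounding matters little.
- If a Wilcoxon signed-rank test were meant, n would be about 54 (normal parent, relative efficiency 3/π = 0.955) to 60 (minimum relative efficiency 0.864). So the choice of test has some bearing on n.

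**3. What would an interval show?**

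Half-width of a 95% confidence interval for the mean change at n = 52: t(0.975, 51)/√52 = 2.008/7.211 = 0.278 SD of the change. An observed change of 0.40 SD would carry an interval of about 0.40 ± 0.28, that is 0.12 to 0.68 SD. A bare mean change would not convey this uncertainty.

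**4. The sections side by side**

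| Outcome | Outcome measurement | Sample size | Phase 2 analysis |
|---|---|---|---|
| Loneliness | secondary; significant reduction | primary; 80% power | descriptive |
| Depression | significant change | – | descriptive |
| Quality of life | significant change | – | not listed |
| Falls self-efficacy | significant change | – | descriptive |
| Physical activity | significant change | – | descriptive |
| Diet | significant change | – | descriptive |
| Feasibility and acceptability | no significance criterion | – | descriptive |

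Only the last row is consistent throughout.

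**The case against.** The best defence is that this is a condensed article about a small pilot. Feasibility and acceptability are central to it, and description is the right method for them. The intended test can largely be recovered from the number 52, and a fuller plan may name it. Quality of life may simply have been compressed, since the abstract groups depression under it.

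Much of this stands. The feasibility and acceptability results are unaffected, the omission of quality of life is minor, and nothing shows that a test would in fact be chosen after the data are seen. What does not stand is the appeal to an unseen plan: the article states a method for these changes, so a plan that named a test would conflict with the published text.

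A reader might infer more than the documents support:

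- **That time trends or regression to the mean undermine the result.** The article does not say that COVID-19 restrictions were easing; it says only that recruitment adapts to them. Phase 2 eligibility has no loneliness threshold that would select extreme baseline scores. The single non-randomised group is declared openly. All that follows is that an uncontrolled change cannot by itself be attributed to the program.
- **That six outcomes at 5% carry a 26% risk of a false positive.** The sum 1 − 0.95⁶ = 0.265 assumes six independent tests, all with no true change. Depression is a dimension of the overall AQoL-8D, so they are not independent. A purely descriptive analysis runs no tests at all.
- **That only about 46 pairs would be analysed.** That is 88% of 52, with the 88% taken from a different study. Here the last observation is carried forward, so as written 52 are analysed.

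**Conclusion.** The plan is wrong as written on this point. It defines six participant-level outcomes by significance and sizes Phase 2 for a test on one of them, then gives five of the six a purely descriptive analysis and the sixth none. The powered question about loneliness has no matching analysis.

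The contradiction rests on the text alone. The link to a particular test rests on two assumptions, a two-sided 5% alpha and d defined on the SD of the change; under them 52 is reproduced exactly. The sample size is not in error. The documents do not support the wider conclusion that the trial's findings as a whole are unsound: the fault is confined to the participant-level outcomes.

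**What to change.** **Data collection and analysis plan, Phase 2.** Keep descriptive statistics for feasibility and acceptability. Add, for example: *The mean pre-post change in De Jong Gierveld score will be estimated with a 95% confidence interval and tested with a two-sided paired t-test at the 5% level. Depression, quality of life, falls self-efficacy, physical activity and diet will be reported as mean change with 95% confidence interval, without claims of significance.*

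**Outcome measurement.** Replace significant reduction and significant changes by change. Add that an uncontrolled pre-post change is preliminary and cannot by itself be attributed to the program.

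**Outcome measurement and Sample size considerations.** Give loneliness the same status, primary or secondary, in both places. State the alpha and sidedness behind 52.

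These changes should be made before post-intervention data are seen. The cost is slightly more analysis and less favourable outcome wording. The sample size stays at 52, because the test named is the one that gives that number.

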### Measures

At baseline, data on participants’ AMD diagnosis such as stage and type of AMD, unilateral or bilateral AMD and details about any treatment received will be collected from the clinic. A pre-post intervention questionnaire will also be administered online via Research Electronic Data Capture (REDCap) to all participants involved in the intervention (Phase 2). The post-intervention questionnaire will be administered immediately after the 10-week intervention period. It will cover topics including: demographics (age, sex, ethnicity, education level, living situation (e.g., living alone or with others; homeowner or renter), marital status, employment status, and usual income); vision function; physical activity level; diet; falls self-efficacy; loneliness; quality of life; and program acceptability and feasibility. Specific instruments included in this questionnaire are described in more detail below.

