The Active Australia Survey is a 13-item, self-administered questionnaire to measure the frequency and duration of recreational physical activity in the last week as well as knowledge about the health benefits of physical activity [23]. The knowledge component of the survey is presented as a five-point Likert scale with response options ranging from ‘Strongly Disagree’ to ‘Strongly Agree’ [23]. This instrument can be implemented via computer-assisted telephone interviewing or in face-to-face interviews and is the recommended Australian population-based physical activity survey [23, 24].The Short Dietary Questionnaire for Age-related Macular Degeneration (SDQ-AMD) was used in the aforementioned telehealth intervention for people with AMD to capture dietary intake in the last week [25]. Response options to each food item is expressed as either serves consumed per day or per week, or number of times consumed per week [25]. The SDQ-AMD was adapted from a validated questionnaire [26] to capture intake of key food groups linked to AMD management. A question about dairy intake has also been added given evidence of a protective association between dairy intake and AMD [27]. The scoring criteria for the SDQ-AMD has been described previously [17] however will also be modified to provide a score for dairy intake.National Eye Institute Visual Function Questionnaire-25 (VFQ-25) is a reliable and valid instrument to capture vision function in people with AMD [28]. This instrument contains questions on the following sub-scales: general health; general vision; expectations; wellbeing/distress; ocular pain; near vision; distance vision; peripheral vision; social function; colour vision; driving; role limitations; and dependency [29]. The VFQ-25 scores are reported as an average of the items within each sub-scale [29].Falls Self-Efficacy Scale–International (FES-I) is a 16-item questionnaire to assess participants’ concerns about their possibility of falling [30]. Response options are presented on a four-point Likert Scale ranging from ‘Not at all concerned’ to ‘Very concerned’. Total scores range from 16 to 64 where a score of 16–19 indicates ‘low concern’; 20–27 is ‘moderate concern’; and 28–62 is ‘high concern’ [30].De Jong Gierveld Loneliness Scale is valid 6-item questionnaire to reliably capture overall, emotional and social loneliness [31]. This scale was similarly used in our WTL-Z RCT among older adults living in the United Kingdom. Scores range from 0 (not lonely) to 6 (extremely lonely). The guide suggests that the following items should be reversed before scoring: “There are plenty of people I feel close to”; “There are many people I can completely trust”; and “There are enough people I feel close to” [31].The Assessment of Quality of Life-8 Dimensions (AQoL-8D) is a 35-item questionnaire that includes eight individually scored dimensions [32]. The AQoL-8D comprises the 6 dimensions within the AQoL-6D (i.e., independent living; relationships; mental health (including depression); coping; pain; and senses) with two additional dimensions (i.e., self-worth; and happiness) [32]. The scoring guide for each dimension have been developed by the researchers at Monash University, Australia who developed the instrument (Assessment of Quality of Life, n.d.). In brief, the score ranges for each dimension are as follows: 4 to 22 (independent living); 7 to 34 (relationships); 8 to 41 (mental health); 3 to 15 (coping); 3 to 13 (pain); 3 to 16 (senses); 3 to 15 (self-worth); and 4 to 20 (happiness) [32].The ‘Attitude to Falls-Related Intervention Scale’ (AFRIS) [33] will be administered pre-post intervention to assess participant acceptability of the program. This will be achieved by comparing the pre-post mean total scores of participants offered the intervention, with possible scores ranging from 6 to 42 i.e., ‘less positive’ to ‘more positive’ attitude towards the intervention [33].

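### With only a baseline and one post-program questionnaire, carrying the last observation forward scores every missing post questionnaire as exactly zero change, which biases the estimated change in an unknown direction

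*Protocol article*

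**What the plan says.** The protocol article, under Data collection and analysis plan (Phase 2), sets one rule for incomplete data: "For missing data, the last observations will be carried forward prior to data analysis". It exempts no outcome and mentions no sensitivity analysis.

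The same section describes the data source: "Data for all participants will be collected via online self-report pre-post questionnaires administered via REDCap". The Measures section fixes the timing of the only follow-up: "The post-intervention questionnaire will be administered immediately after the 10-week intervention period". No interim questionnaire is described.

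The rule covers both purposes of the pilot. For preliminary efficacy, the analysis section describes "the pre-post intervention changes in loneliness, depression, falls self-efficacy, physical activity, and dietary intakes". Under Sample size considerations, loneliness is the outcome on which the target of 52 rests. For acceptability, the Measures section says that AFRIS "will be administered pre-post intervention to assess participant acceptability of the program", by "comparing the pre-post mean total scores of participants offered the intervention". People who were offered the program and did not return the second questionnaire are therefore within its scope.

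**The concern.** Carrying the last observation forward (LOCF) is usually described for designs with several visits, where the carried value already reflects some time on treatment. Here the last value before a missing post score can only be the baseline. The rule thus assumes, for each participant without a post questionnaire, that nothing changed on any pre-post scale.

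Two things are at stake. First, the mean change in loneliness is wrong unless the missing participants really did not change on average, and the sign of the error depends on what happened to them. A pilot's effect estimate is commonly used to plan a later trial, and this protocol itself took its 0.4 from earlier work. Second, post-program AFRIS is meant to record attitude after experiencing the program. For a missing participant, it would record an attitude formed before the first session.

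**Working it through.** **Inputs**
- N = 52, effect size 0.4, power 80% (Sample size considerations).
- Two measurement occasions (Measures; Data collection and analysis plan).
- Share missing, m: not stated for this trial. The same sample size section cites 88% retention in an earlier trial, so m = 12% (about 6 of 52) is an assumption, with 20% (about 10 of 52) as a less favourable case.
- Units are the SD of the pre-post change. Positive values mean improvement.

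**The plan's own figure.** A paired t-test with d = 0.4 and 80% power, at an assumed two-sided alpha of 0.05 (the article states no alpha), gives n = 52 with power 0.808. The stated 52 reproduces, with no allowance for missing questionnaires.

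**Formulas.** Let observed participants improve by 0.40 on average and let missing participants truly change by δ.
- True mean: (1 − m) × 0.40 + m × δ
- LOCF mean: (1 − m) × 0.40 + m × 0 = (1 − m) × 0.40
- Bias of LOCF: −m × δ
- Bias of an observed-only mean: m × (0.40 − δ)

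LOCF understates benefit when δ is above zero, overstates it when δ is below zero, and is unbiased only at δ = 0.

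**Case A: missing participants changed like the others (δ = 0.40, truth 0.40)**
- 6 of 52 missing: 46 × 0.40 / 52 = 0.354, bias −0.046. By exact share, 0.88 × 0.40 = 0.352.
- 10 of 52 missing: 42 × 0.40 / 52 = 0.323, bias −0.077. By exact share, 0.80 × 0.40 = 0.320.
- Simulated coverage of a nominal 95% interval (40,000 trials, normally distributed changes): about 93.6% with 6 missing and about 91% with 10 missing.

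**Case B: missing participants worsened by 0.4 (δ = −0.40)**

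| Missing | True mean | LOCF mean | LOCF overstates by | Observed-only mean | Observed-only overstates by |
|---|---|---|---|---|---|
| 6 of 52 | (46 − 6) × 0.40 / 52 = 0.308 | 0.354 | 46/40 − 1 = 15% | 0.40 | 52/40 − 1 = 30% |
| 10 of 52 | (42 − 10) × 0.40 / 52 = 0.246 | 0.323 | 42/32 − 1 = 31% | 0.40 | 52/32 − 1 = 62.5% |

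By exact shares, the LOCF overstatement is 0.88/0.76 − 1 = 16% and 0.80/0.60 − 1 = 33%.

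**Standard error.** In Case A, the SD of change after LOCF is √[(1 − m)(1 + 0.16m)] = 0.947 at m = 0.12. The reported SE is 0.947/√52 = 0.131. The actual sampling SD of the LOCF mean with 6 fixed zeros is √46/52 = 0.130. The SE is smaller than that for 46 completers (1/√46 = 0.147), but it is right for the estimator that it describes. Coverage falls mainly because the estimate is off centre.

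**Power.** Simulated power is 0.76 for both LOCF and completers with 6 missing, and 0.72 for both with 10 missing.

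**The case against.** The strongest defence is that the harm is modest at the only retention figure in the document, and that the obvious alternatives are not uniformly better. With 6 missing, the bias in Case A is about 0.05 SD and coverage loses about 1.4 percentage points. In that case LOCF even has the smaller root mean square error: √(0.046² + 0.130²) = 0.138, against 0.147 for completers. In Case B, an observed-only analysis overstates benefit about twice as much as LOCF. So would a mixed model on observed scores if missingness did not depend on baseline. The plan is also mainly descriptive and specifies no interval, although the Outcome measurement section does look for significant changes. All of this stands. It limits the size of the point and shapes the remedy. It does not make a fixed assumption of zero change a sound main analysis.

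Some stronger readings are tempting but not supported:
- **That the interval is too narrow because zeros shrink the SD.** The SE is correct for the LOCF mean; bias is the main reason for the lost coverage.
- **That acceptability is overstated.** The documents do not say that baseline attitudes are favourable or that leavers are dissatisfied. Because AFRIS is judged by pre-post comparison, a carried baseline pulls any shift, in either direction, toward zero. Attendance, reasons for missed sessions, attrition and satisfaction are reported separately, so acceptability does not rest on AFRIS alone.
- **That every dropout is imputed.** Only participants without a post questionnaire are. Someone who stops attending but returns the form is not, and staff prompt participants to return it.
- **That the feedback form is affected in the same way.** It is given only after the program, so it has no baseline to carry.
- **That the rule costs power.** Power equals that of completers.

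**Conclusion.** The point holds. The rule is stated outright and, in a two-occasion design, can only mean baseline carried forward, with zero change for each missing post questionnaire on every pre-post scale, AFRIS included. A separate analysis plan could add sensitivity analyses, but it would have to reverse this sentence to change the main analysis.

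The direction of the error cannot be known in advance, so LOCF cannot be defended as conservative. For a 0.40 SD improvement among those observed, the error runs from attenuation to about 0.35 SD up to a 15% overstatement at 12% missing, and from attenuation to 0.32 SD up to a 31–33% overstatement at 20%. These ranges rest on two assumptions that the protocol does not supply: the share missing, and a change among missing participants between an improvement of 0.4 SD and a worsening of 0.4 SD. The identity of LOCF with zero change needs neither assumption.

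**What to change.** Replace the missing-data sentence in the Phase 2 analysis plan with wording to this effect:

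- Pre-post change is estimated from all observed scores of all enrolled participants with a linear mixed model, or with multiple imputation using baseline score, age, vision function and number of sessions attended. It is reported with a 95% confidence interval and the number missing.
- Baseline carried forward is kept only as a labelled sensitivity analysis.
- A second sensitivity analysis assumes that missing participants worsened, for example by shifting the imputed values. This one is needed because an observed-data analysis overstates benefit more than LOCF in that situation.
- Post-program AFRIS is not imputed from baseline. Observed scores and the number missing are reported, with a sensitivity analysis that assumes less favourable scores for those missing.

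The change uses only data already planned for collection. It costs a paragraph of wording, a little more analysis work and a slightly wider interval.
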